## Abstract

**Background:**

Contrast-induced nephropathy (CIN), an acute kidney injury resulting from the administration of intravascular iodinated contrast media, is an important cause of morbidity/mortality following coronary angiographic procedures in high-risk patients. Despite preventative measures intended to mitigate the risk of CIN, there remains a need for an effective intervention. Remote ischaemic conditioning (RIC), where non-injurious ischaemia is applied to an arm prior to the administration of contrast, has shown promise in attenuating CIN but its effectiveness in preserving long-term renal function is unknown, which will be studied as part of the effect of remote ischaemic conditioning against contrast-induced nephropathy (ERICCIN) trial. (http://Controlled-trials.com Identifier: ISRCTN49645414.)

**Methods:**

The ERICCIN trial is a single-centre, randomised double-blinded placebo-controlled trial which plans to recruit 362 patients who are at risk of CIN, defined by pre-existent renal impairment (estimated glomerular filtration rate <60 ml/min/1.73 m^2^), over a period of 2 years. Patients will be randomised to either control or RIC consisting of 4, 5 min 200 mmHg balloon-cuff inflation/deflations, to the upper arm. The primary endpoint will be the development of CIN (>25 % of eGFR, or rise of creatinine of >44 μmol/l) at 48 h. A key secondary endpoint will be whether RIC impacts upon persistent renal impairment over the 3-month follow-up period. Additional secondary endpoints include the measurement of serum neutrophil gelatinase-associated lipocalin and urinary albumin at 6, 48 h and 3 months following administration of contrast.

**Implications:**

Findings from ERICCIN trial will potentially demonstrate that RIC attenuates contrast-induced acute and chronic kidney injury and influence future clinical practice guidelines in at-risk patients undergoing coronary angiographic procedures.

## Background

Contrast-induced nephropathy (CIN) is an acute, iatrogenic kidney injury triggered by the intravascular administration of iodinated contrast agents. Defined as a 25 % rise or an absolute 0.5 mg/dl (44 μmol/L) increase in serum creatinine within 72 h of contrast exposure, in the absence of an alternative explanation [1], CIN is an important clinical problem following angiography and percutaneous intervention. It represents the third most common cause of hospital-acquired acute renal failure [2, 3] and is associated with significant mortality and morbidity, with up to 19 % of those suffering CIN developing persistent renal impairment months after contrast media exposure [4]. With the incidence of renal replacement therapy estimated at 0.2 % [5], the attendant healthcare costs associated with CIN are substantial [5]. Moderate to severe chronic renal impairment (estimated glomerular filtration (eGFR) <60 ml/min or a creatinine of >120 mmol/L; National Kidney Foundation chronic kidney disease (CKD) stages 3 and 4 [6]) is regarded as the most important risk factor in the development of CIN [7], but other risk factors such as diabetes, reduced left ventricular systolic function, advancing age, concomitant use of nephrotoxic drugs, large contrast agent volumes, intraprocedural hypotension and either high or low haematocrits (dehydration/anaemia) are also well recognised [8]. Due to the association between renal and cardiovascular disease, patients with CIN risk factors are common within the cohort of patients requiring an angiographic intervention and, despite the introduction of a number of prophylactic measures, the incidence of CIN remains unacceptably high. In the CARE study, the incidence of CIN despite optimal medical therapy remained between 10 and 15 % [9]. The notion of optimal medical care in this patient cohort remains hotly contested. There are a number of national and international guidelines and all recommend avoidance of nephrotoxic drugs, adequate pre-hydration and the use of low- or iso-osmolar contrast agents. The augmentation of pre-hydration with antioxidants or alkalinizers such as *N*-acetyl cysteine and sodium bicarbonate, respectively, remain hotly contested, but recent meta-analyses appear to suggest a small advantage towards bicarbonate pre-hydration over *N*-acetylcysteine [10]. Given a lack of clarity regarding the most efficacious intervention against CIN, a large, multicentre randomised control study has started recruiting (target 8,680 patients, the prevention of serious adverse events following angiography (PRESERVE) trial [11]), the results of which will hopefully help to clarify optimal preparation of patients at risk of CIN. Similarly, there is debate over which contrast media is the least injurious to the at-risk kidney. The landmark comparison trial between iso-osmolar iodixanol and the low-osmolar iohexol contrast media by Chalmers and Jackson in 1999, which demonstrated a modest superiority for iodixanol, has been a powerful influence on subsequent contrast media decision-making, although more recent meta-analyses seem to suggest parity of risk between iso-osmolar and the majority of low-osmolar contrast media [12–16]. The lack of clear evidence of one intervention over another appears to suggest one thing: the lack of a single successful intervention to prevent CIN. There is, therefore, a clear clinical need for an effective intervention that can reduce the incidence of CIN following angiographic and other iodinated contrast requiring procedures.

While the pathophysiology of contrast-induced renal injury remains the subject of on-going basic research, one of the principal mechanisms for acute contrast nephropathy is thought to be vaso-constrictive renal hypoxic injury and release of reactive oxygen species (ROS) [17]. Such an injury is likely to be mediated by cell-death signalling of the type found in many other organ systems typified by lethal reperfusion injury [18]—and as such may be amenable to interventions such as ischaemic preconditioning (see review [19]). Interestingly, the potential of remote ischaemic conditioning was highlighted in a retrospective study by Whittaker and Przyklenk [20], and more recently three prospective trials have been published to support the supposition of remote renoprotection. In the first, Er et al. demonstrated in a small (*n* = 50/group) proof-of-concept trial that remote ischaemic conditioning (RIC), consisting of 4 cycles of 5 min ischaemia/5 min reperfusion of the upper limb by inflation/deflation of a blood pressure cuff prior to contrast exposure, was effective in significantly reducing the rate of CIN from 40 % in controls to 12 % [21]. The second, Deftereos et al. recruited 225 non-ST elevation myocardial infarction (NSTEMI) patients to receive either sham or an ischaemic conditioning stimulus consisting of 4, 30 s ischaemia/30 s reperfusion cycles by inflation/deflation of an intracoronary balloon following intervention upon the culprit lesion; consistent with upper limb RIC, they demonstrated that intracoronary RIC reduced the rate of CIN from 29.5 % in control to 12.4 % [22]. The third, Igarashi et al. [23], using an identical conditioning regime to that used by Er et al. and, utilising a novel bio-marker, urinary liver-type fatty acid-binding protein (L-FABP) as a primary endpoint, demonstrated a significant reduction of CIN from 26.9 to 7.7 % in the remote ischaemic preconditioned group. Although a small trial (*n* = 20 per group), there was an attempt to uncover the mechanism of contrast media renal injury, with the demonstration of attenuated oxidative stress as measured by derivatives of reactive oxidative metabolite (D-ROM) levels and reduced asymmetrical dimethylarginine (ADMA), an endogenous inhibitor of nitric oxide synthase following remote ischaemic preconditioning. These data are encouraging, but there is a need for further evidence before routine medical practice can be altered. These previous proof-of-concept trials have been small and relatively limited in scope, concentrating primarily upon the incidence of acute kidney injury and have not looked at the longer-term sequelae of that renal injury in terms of persistent renal damage. As noted above, CIN is not a purely transient phenomenon; it frequently has long-term serious sequelae with persistent kidney damage evident in a fifth of those with an acute biochemical manifestation of CIN [4]. The effect of remote ischaemic conditioning against contrast-induced nephropathy (ERICCIN) trial is therefore designed to evaluate RIC against CIN in elective angiography/PCI, and to ascertain the longer-term efficacy in terms of prevention of persistent renal injury at 3 months determined by serum creatinine/estimate glomerular filtration rate and development of proteinuria, a known consequence of CIN [24] and a portent for increasing cardiovascular risk and all-cause mortality [25].

## Methods

### Study objectives

The primary objective of this study is to determine whether remote ischaemic conditioning attenuates the rate of CIN arising from the administration of iodinated intracoronary contrast as part of routine and semi-emergent (NSTEMI) coronary artery angiography/percutaneous intervention. The study will ascertain whether acute injury at 48 h following the administration of contrast, as determined by serum creatinine, serum neutrophil gelatinase-associated lipocalin (NGAL, determined by both laboratory and point-of-care testing) and new-onset proteinuria, is attenuated by remote ischaemic conditioning. The study will also seek to ascertain whether attenuation of contrast-induced nephropathy results in chronic kidney damage defined by persistently depressed glomerular filtration rate and increased or new-onset proteinuria.

### Study design

The study has received Ethical Committee approval (National Research Ethics Service Committee, London-Queen Square; REC reference 13/LO/0502). The ERICCIN trial is a placebo-controlled, single-centre double-blind proof-of-concept study. It investigates the effect of remote ischaemic conditioning upon acute renal injury at 48 h and as a secondary endpoint, to determine whether it impacts upon long-term renal function 3 months post-procedure.

### Study population

The investigators will seek to recruit patients aged between 18 and 85 years of age and scheduled for any Cardiac Catheter Laboratory investigation that involves the administration of intracoronary iodinated contrast at the Heart Hospital, UCLH NHS Trust (Fig. 1). The patients recruited will have an estimated glomerular filtration rate (as estimated using the modification of diet in renal disease (MDRD) formula [26]) of less than 60 ml/min/1.73 m^2^ and will have freely given informed consent. Patients excluded from the trial will fall outside these pre-requisites, and in addition will have one or more of the following exclusion criteria: pregnancy; end-stage renal failure and on dialysis; coagulopathy with an INR >2.0; recent intravenous or intra-arterial iodinated contrast exposure within the previous 4 weeks; any contraindication for balloon-cuff inflation or have presented as an ST elevation myocardial infarction, cardiac arrest or are in cardiogenic shock.

**Fig. 1 Fig1:**
[figure not shown]
Flow diagram showing the recruitment and design of the ERICCIN trial. Patients meeting the inclusion criteria, and having provided informed consent are then randomised to either placebo (non-occlusive low-pressure inflation of the blood pressure cuff to 15 mmHg) or treatment with RIC (200 mmHg cuff-inflation). Each 5 min inflation/5 min deflation is repeated over 4 cycles. Blood samples are drawn for biochemical assessment at baseline (pre-treatment), at 6 h, at 48 h and at 3 months. At these time points, urine samples are also taken for urinary protein assessment

The study will conform to the spirit and letter of the declaration of Helsinki and in accordance with the UCL Good Clinical Practice Guidelines.

### Intervention

The remote ischaemic conditioning intervention will be undertaken within 2 h prior to the administration of iodinated contrast media. Those patients randomised to receive RIC will have a standard blood pressure cuff placed on the upper arm. The administration of the intervention will be via the automated delivery of four cycles of 200 mmHg blood pressure cuff inflation for 5 min followed by cuff deflation for 5 min, using a laptop-controlled device developed and purpose built within the department of Medical Physics and Bioengineering at UCL. The placebo group will receive a sham protocol similar to RIC, but rather than the cuff being inflated to 200 mmHg to induce transient limb ischaemia, the cuff is instead inflated to a non-occlusive 10 mmHg to provide the impression of a treatment being administered.

### Randomisation and allocation

On the day of the angiographic procedure, the patients will be randomised to one of two groups: remote ischaemic conditioning or control, using minimization for CIN risk factors in a 1:1 ratio. The minimization criteria are those factors which predict the risk of acute kidney injury: eGFR (<20, 20–40, 40–60 ml/min), age (<75, >75 year), diabetes, NYHA III/IV heart failure and haematocrit (<0.39, >0.39) as identified by Mehran et al. [8], and whether the patient is undergoing bi-ventricular device implantation, a recognised high-risk group for CIN [27]. This will ensure that the study and placebo groups are evenly matched in terms of the pre-procedure risk of CIN. Randomisation will be performed by a non-blinded cardiac research nurse using a freeware computer programme (MinimPy 0.3).

## Study endpoints

### Primary clinical endpoint

The primary endpoint of the trial will be the incidence of contrast-induced nephropathy, as defined biochemically by a 25 % increase or an absolute rise of 0.5 mg/dl (44 μmol/l) from baseline in serum creatinine 48 h following contrast medium exposure.

### Secondary clinical endpoints

The secondary endpoint of the study will be the demonstration of a persistent benefit of the RIC intervention against long-term renal impairment. The renal function will be determined by biochemical markers: creatinine, eGFR and serum NGAL from baseline at 6, 48 h and 3 months post-contrast exposure. These data will be further supported by the measurement urinary albumin (dipstick and Albumin:Creatinine ratio) from baseline at 48 h and 3 months post-contrast medium exposure as a measure of renal tubular function.

In addition to biochemical assessment of renal function, for all groups the cardiovascular endpoints include death, non-fatal MI, revascularisation, acute heart failure, non-fatal stroke, major haemorrhage, rehospitalisation, haemofiltration or haemodialysis during 3 months follow-up will also be recorded.

### Sample size calculation

There will be two arms to the ERICCIN trial: placebo control and remote ischaemic conditioning. We plan to recruit 362 patients (181 per arm of the study), undergoing angiographic procedures at the Heart Hospital, UCL. The rate of CIN in previous trials has ranged from 7 % [8] to 40 % [21] (Table 1), with a mean and median reported rate of CIN of 19 and 17 %, respectively. These data are in-line with our own audit data of 1,913 patients undergoing angiographic procedures at the Heart Hospital over the period of 1st June 2011 to the 30th June 2012, revealing a rate of CIN of 22 % over the study period (unpublished data). For our study calculations, we proposed a CIN incidence of 15 %.

**Table 1 Tab1:** Summary of CIN incidence in published clinical trials

Study	Number of patients recruited	Incidence of contrast nephropathy in control group (%)
RenPro [21]	100	40
Renoprotective effect of RIC [22]	225	29.5
Iloprost prevents CIN [29]	208	22
Cystatin-C and CI-AKI [35]	410	21.2
Persistent renal damage after CI-AKI [4]	3,986	12.1
CARE study [9]	482	10
REMEDIAL trial [28]	326	9.9
Urinary IL-18 and NGAL as early predictive markers [36]	150	8.7

Citations are listed in order of cited CIN incidence

Two previous studies have evaluated RIPC and its effect on CIN, reporting between 58 % [22] and 70 % [21] reduction of acute kidney injury. For our power calculations, we have proposed an effect at the lower end of this range, and have powered our study to determine a difference of 60 %. For a power of 80 % and a significance level of 0.05, we would need to recruit 181 patients into each trial arm, 362 patients in total.

### Statistical analysis

The effect of remote ischaemic conditioning on CIN will be evaluated using logistic regression. This will be adjusted for the minimization factors, as well as other covariates of interest (gender, volume/type of contrast, peri-procedural hypotension and intra-arterial balloon pump use).

The effect of RIPC treatment on serum creatinine, eGFR and urine ACR compared with baseline, at 48 h and 3 months will be evaluated using a repeated measures mixed effects model. The effect on serum NGAL compared with baseline at 6, 48 h and 3 months will be evaluated using the same model. The treatment effect will be adjusted for minimization factors and other covariates of interest (gender, volume/type of contrast, peri-procedural hypotension and intra-arterial balloon pump use.) A Bonferroni correction will be applied to eGFR ranges (<20, 20–40, 40–60 ml/min). The data analysis will be performed in a blinded fashion, on an intention-to-treat basis.

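### Elective versus NSTEMI presentation is neither balanced nor adjusted for, while the models spend a term on balloon pump use, which is post-randomisation and probably sparse; swapping the two is a small, cheap gain

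*Protocol article*

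**What the plan says.** **Population.** Study objectives (Protocol article) covers "routine and semi-emergent (NSTEMI) coronary artery angiography/percutaneous intervention", and the Discussion likewise names elective and semi-emergent procedures. The last sentences of the Background describe the trial as one in elective angiography/PCI only. Study population excludes patients who "have presented as an ST elevation myocardial infarction, cardiac arrest or are in cardiogenic shock".

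**Allocation.** Randomisation and allocation lists six minimisation factors: eGFR band, age, diabetes, NYHA III/IV heart failure, haematocrit and bi-ventricular device implantation. It adds: "This will ensure that the study and placebo groups are evenly matched in terms of the pre-procedure risk of CIN".

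**Models.** Statistical analysis adjusts the primary logistic regression for the minimisation factors and for "other covariates of interest (gender, volume/type of contrast, peri-procedural hypotension and intra-arterial balloon pump use". The repeated measures mixed models carry the same list. Presentation is in neither place.

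**Rates.** The Background reports, for a cited trial of 225 NSTEMI patients, that "intracoronary RIC reduced the rate of CIN from 29.5 % in control to 12.4" per cent. Sample size calculation states: "For our study calculations, we proposed a CIN incidence of 15" per cent.

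**The concern.** Presentation splits the enrolled population in two and is known at screening. The one NSTEMI rate that the article cites is about twice the planning rate (29.5/15 = 1.97). If presentation is prognostic, the assurance of matched pre-procedure risk does not cover it, and a chance imbalance would go unadjusted. The article already adds one procedure-type factor, bi-ventricular device implantation, because it marks a high-risk group. The same reasoning would admit presentation.

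Meanwhile a model with few events gives a term to balloon pump use. Patients are randomised on the day of the procedure and conditioning precedes contrast, so in general this variable arises after randomisation. Adjusting for it conditions the intention-to-treat effect on something that happens after allocation. Few users are likely once shock, cardiac arrest and STEMI are excluded. At stake are a little power and the stability of the primary model.

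**Working it through.** **1. The plan's own sample size.** Inputs from Sample size calculation: control rate 15%; a relative reduction, "have powered our study to determine a difference of 60" per cent, so 15% versus 6%; "For a power of 80 % and a significance level of 0.05". Sidedness is not stated; two-sided reproduces the figure. With mean rate 0.105:

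n = [1.960 × √(2 × 0.105 × 0.895) + 0.842 × √(0.15 × 0.85 + 0.06 × 0.94)]² / 0.09² = 180.9, so 181 per arm, as stated.

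**2. Events against parameters.** Expected events: 181 × 0.15 + 181 × 0.06 = 27.2 + 10.9 = 38. Parameters, taking contrast volume as linear and contrast type as two levels: treatment 1, eGFR 2, age 1, diabetes 1, NYHA 1, haematocrit 1, bi-ventricular device 1, gender 1, contrast volume 1, contrast type 1, hypotension 1, balloon pump 1. That is 13, or 38/13 = 2.9 events per parameter.

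**3. Balloon pump use.** The article gives no frequency; 0.5 to 3% is assumed. With use p and CIN risk r among users, the chance that no user has CIN is (1 − p × r)^362. In that case the logistic coefficient has no finite estimate.

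| Assumed use | Expected users of 362 | No CIN among users, r = 10.5% (trial average) | r = 50% |
|---|---|---|---|
| 0.5% | 1.8 | 83% | 40% |
| 1% | 3.6 | 68% | 16% |
| 3% | 10.9 | 32% | 0.4% |

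This applies to the logistic model. In the mixed models the term is not subject to this failure, and the objection there is its timing.

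**4. Chance imbalance in presentation.** The NSTEMI share f is not in the article and is assumed. Control CIN is set at 29.5% in NSTEMI, and the rate in the rest is chosen so that the control mean is 15%.

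- Imbalance SD = √(2f(1 − f)/181).
- Shift SD with no treatment effect = imbalance SD × gap between the strata.
- With a 60% reduction in both strata, the treated-arm gap is 0.4 of the control gap, so the average gap is (1 + 0.4)/2 = 0.7 of it.
- Share of outcome variance explained = f(1 − f) × gap² / (0.15 × 0.85).

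| f | Rate in the rest | Gap (points) | Imbalance SD (points) | Chance of more than 5 points | Shift SD, no effect | Shift SD, planned effect | Variance explained |
|---|---|---|---|---|---|---|---|
| 10% | 13.4% | 16.1 | 3.2 | 11% | 0.5 | 0.4 | 2% |
| 20% | 11.4% | 18.1 | 4.2 | 23% | 0.8 | 0.5 | 4% |
| 30% | 8.8% | 20.7 | 4.8 | 30% | 1.0 | 0.7 | 7% |
| 40% | 5.3% | 24.2 | 5.1 | 33% | 1.2 | 0.9 | 11% |

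Standard error of the CIN difference: √[(0.1275 + 0.0564)/181] = 3.2 points under the planned effect, and √(2 × 0.1275/181) = 3.75 with no effect. At f = 30% the like-for-like comparisons are therefore 0.7 against 3.2, or 1.0 against 3.75.

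**5. Power from adjusting.** This uses the expected information of a logistic model with treatment and presentation only. The odds ratio for presentation is taken from 29.5% versus an assumed 10%: (0.295/0.705)/(0.10/0.90) = 3.77. Arm rates are held at 15% and 6%.

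- Without presentation: log odds ratio −1.017, SE 0.376, Wald power 77.2%. This is below 80% because the Wald test differs from the test in step 1.
- With presentation, f = 30%: −1.060, SE 0.384, power 78.9%.
- Across f = 10 to 50%: 78.3 to 78.9%, a gain of 1.1 to 1.7 points.

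**The case against.** **The factor may not be prognostic.** A reader might infer that the article's own figures show a much higher CIN rate in NSTEMI. They do not. The 29.5% is one control arm in another trial. A cuff trial not described as NSTEMI had 40%. The Discussion attributes both rates most likely to the risk profile of the patients recruited. The trials near 10% are not labelled elective, the hospital's 22% audit rate is not split by presentation, and the Background's list of CIN risk factors omits NSTEMI. This objection stands; the figure is suggestive only.

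**Omission is not bias.** A reader might also treat chance imbalance as an extra hazard. Under randomisation it averages to zero and is already contained in the standard error and the type I error. This stands too. What remains is a small gain in power and in conditional balance.

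**The gain may be smaller still.** The power calculation includes no other covariates. If presentation correlates with eGFR, age, diabetes, heart failure or haematocrit, part of the gain and part of the balance are already obtained. The NSTEMI share may also be low. Both are fair.

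**The sparsity is inferred.** No balloon pump frequency is given. The inference from the exclusions is reasonable, but it is not a documented figure.

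**It is only a choice of covariate, and the swap leaves other post-randomisation terms.** It is true that contrast volume and peri-procedural hypotension share the timing problem, so the fix must deal with them as well. But a baseline factor in place of a sparse post-randomisation one is better at the same parameter count, so the worry about overloading the model does not apply to the swap.

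**Conclusion.** The point holds as a minor improvement. Presentation is a pre-randomisation feature of the enrolled mix that the plan neither balances nor adjusts for, and the assurance about matched pre-procedure risk does not extend to it. Balloon pump use is a poor occupant of a model with about 2.9 events per parameter: it arises after randomisation and may well have no finite coefficient.

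The size is small: about 1 to 2 points of power, and a shift SD of about 0.7 point against a standard error of 3.2 under the planned effect. These figures rest on an assumed NSTEMI share (10 to 50% for power, 30% for the shift), on the single cited NSTEMI rate carrying over to this trial and, for power, on an assumed 10% in other patients. Neither the validity of the randomised comparison nor the 181 per arm is in question.

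**What to change.** 1. In the primary logistic model and the mixed models, remove balloon pump use and put presentation (elective versus NSTEMI) in its place. The count stays at about 13 parameters.
2. Move contrast volume and peri-procedural hypotension, also post-randomisation, to a sensitivity analysis. The primary model then has about 11 parameters, or 38/11 = 3.5 events per parameter.
3. Optionally, and only if recruitment has not begun, add presentation as a binary minimisation factor. If it is not added, limit the statement about matched pre-procedure risk to the listed factors.
4. Reconcile the elective-only description in the Background with Study objectives and the Discussion.

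Cost: a wording change to the analysis, made before unblinding, using a variable already known at screening. The optional step needs one more field in the minimisation set-up and slightly weakens balance on the other factors.

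### Sampling times for the secondary renal markers conflict between sections (6 h creatinine/eGFR and urinary albumin), and the mixed models list no continuous baseline value of the marker as a covariate

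*Protocol article*

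**What the plan says.** All references are to the protocol article.

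- **Secondary clinical endpoints** names "creatinine, eGFR and serum NGAL from baseline at 6, 48 h and 3 months post-contrast exposure". For urine it names "urinary albumin (dipstick and Albumin:Creatinine ratio) from baseline at 48 h and 3 months", without 6 h.
- **Abstract, Methods** lists "serum neutrophil gelatinase-associated lipocalin and urinary albumin at 6, 48 h and 3 months" as additional secondary endpoints.
- **Fig. 1 legend** has blood drawn at baseline, 6 h, 48 h and 3 months, and adds: "At these time points, urine samples are also taken for urinary protein assessment".
- **Statistical analysis** treats three markers together: "serum creatinine, eGFR and urine ACR compared with baseline, at 48 h and 3 months will be evaluated", by means of a mixed model for repeated measurements. NGAL has its own sentence: "The effect on serum NGAL compared with baseline at 6, 48 h and 3 months will be evaluated using the same model".
- The same section lists the adjustment terms: the minimisation factors, gender, contrast volume and type, peri-procedural hypotension and balloon pump use. According to **Randomisation and allocation**, renal function is a minimisation factor in three eGFR bands (below 20, 20–40, 40–60 ml/min). Baseline NGAL and baseline ACR are in neither list.

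**The concern.** There are two linked problems in the same two sentences of the analysis section.

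First, the sampling times differ by section. Condensation into an article does not explain this, because the analysis section gives marker-specific times: it keeps 6 h for NGAL and leaves it out for creatinine and eGFR. If 6 h creatinine is a secondary measure without a stated analysis, whether and how to report it can be settled after the values are seen. Blinded analysis reduces that risk but does not remove it, since a difference between two masked groups is still visible.

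Second, the article does not say how each patient's own baseline enters the models. If it enters as a simple change from baseline, the estimate is less precise than one that adjusts for the continuous baseline, and it carries any chance baseline imbalance between arms. That matters most for NGAL and ACR, which are not minimised. These models carry the 3-month renal comparison, which the abstract calls a key secondary endpoint.

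**Working it through.** **Step 1. The sampling times side by side**

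| Marker | Abstract | Fig. 1 legend | Secondary clinical endpoints | Statistical analysis |
|---|---|---|---|---|
| Creatinine, eGFR | no 6 h value named | blood at 6 h, 48 h, 3 months | 6 h, 48 h, 3 months | 48 h, 3 months |
| Serum NGAL | 6 h, 48 h, 3 months | blood at 6 h, 48 h, 3 months | 6 h, 48 h, 3 months | 6 h, 48 h, 3 months |
| Urinary albumin/ACR | 6 h, 48 h, 3 months | urine at the blood times, so 6 h included | 48 h, 3 months | 48 h, 3 months |

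Only NGAL is consistent throughout. For creatinine and eGFR, the endpoint section conflicts with the analysis section. For urine, the abstract and figure conflict with the endpoint and analysis sections, which agree with each other.

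**Step 2. The plan's own figure**

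The only design figure is the sample size. Inputs from Sample size calculation: control rate 15%, relative reduction 60% (so 6%), power 80%, significance level 0.05 (taken as two-sided). With the pooled-variance formula:

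- pooled rate (0.15 + 0.06)/2 = 0.105
- 1.960 × √(2 × 0.105 × 0.895) = 0.850
- 0.842 × √(0.15 × 0.85 + 0.06 × 0.94) = 0.361
- n = (0.850 + 0.361)² / 0.09² ≈ 181 per arm, 362 in total.

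The figure reproduces. It concerns the binary primary endpoint and does not depend on this point.

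**Step 3. Change score against baseline adjustment, no other covariates**

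Assume equal variance σ² at baseline and follow-up, and correlation r. The documents do not give r. The treatment-effect variance is proportional to:

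- change from baseline: 2σ²(1 − r)
- continuous baseline as covariate: σ²(1 − r²)
- ratio, adjusted to change: (1 − r²) / (2(1 − r)) = (1 + r)/2.

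| Assumed r | Adjusted | Change | Variance ratio | SE of change score larger by |
|---|---|---|---|---|
| 0.7 | 0.51 | 0.60 | 0.85 | 8% |
| 0.8 | 0.36 | 0.40 | 0.90 | 5% |
| 0.9 | 0.19 | 0.20 | 0.95 | 3% |

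At lower assumed correlations the ratio is 0.75 (r = 0.5) and 0.65 (r = 0.3).

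**Step 4. eGFR with the planned bands in the model**

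Baseline eGFR was simulated as normal, truncated to 10–60, with assumed mean/SD of 45/10, 48/9 and 42/12. The three bands were fitted as covariates. The SE of the change score relative to the model that adds continuous baseline was:

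| Assumed r | Ratio across the three settings |
|---|---|
| 0.7 | 1.022 to 1.037 |
| 0.8 | 1.014 to 1.024 |
| 0.9 | 1.007 to 1.012 |

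So the loss for eGFR is about 1–4% in SE. The bands already absorb part of the baseline information. No such band exists for NGAL or ACR, so for them step 3 is the nearer guide, with r unknown.

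**The case against.** The strongest reply is that the baseline part concerns model parameterisation, which an article may leave to a fuller document. The analysis section compares outcomes with baseline in a repeated measures model, so baseline enters in some form. If it is a repeated outcome with a mean common to both arms, precision essentially matches covariate adjustment. This stands to the extent that a reader might infer the models ignore continuous baseline; the text does not establish that. It equally does not support the far larger losses that would follow if follow-up values were modelled with the bands alone. What remains is that the article does give a covariate list, that no marker's own baseline is on it, and that the role of baseline is left open.

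A reader might also infer that three of four markers lose a planned 6 h analysis. That overcounts. eGFR is calculated from creatinine by the MDRD formula (Study population), so these are one measurement. For ACR, the model drops nothing that the endpoint section defines.

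It is also fair to say that the secondary endpoint is persistent benefit, on which 6 h creatinine says little, that the Discussion gives a 6 h rationale only for NGAL, and that a 6 h creatinine analysis would be visibly outside the stated model. These points limit the consequence. They do not remove the conflict between the endpoint and analysis sections.

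Finally, a change score adjusted for banded baseline is valid. The bands make the adjustment incomplete, not wrong.

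**Conclusion.** The point holds in this form. The sampling times conflict on the page: creatinine/eGFR at 6 h between the endpoint and analysis sections, and urinary albumin at 6 h between the abstract and Fig. 1 on one side and the endpoint and analysis sections on the other. In addition, the listed covariates do not include each marker's own continuous baseline, and the way baseline enters the models is not stated.

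The size is modest. Variance reductions of 10%, 25% or 35% might be read off (1 + r)/2 at r = 0.8, 0.5 and 0.3, but they require a pure change score, no other covariates and correlations that the documents do not give. They should not be quoted as the loss in this trial. For eGFR the loss is about 1–4% in SE under assumed r of 0.7–0.9 and the assumed baseline distributions. For NGAL and ACR it is probably larger but cannot be computed from the documents. Leaving 6 h creatinine out of the model should cost little precision at 48 h or 3 months. The primary endpoint and the sample size are untouched.

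**What to change.** 1. Reconcile the sampling times for creatinine/eGFR and urinary albumin in the abstract, the Fig. 1 legend, Secondary clinical endpoints and Statistical analysis. For urine, state whether 6 h is an endpoint, since two sections say one thing and two the other.
2. Add 6 h creatinine/eGFR to the mixed model, as is already planned for NGAL, or declare the 6 h values descriptive.
3. Fit each mixed model to the post-baseline values, with that marker's continuous baseline as a covariate in addition to the planned factors, and say so in the text.
4. Preferably analyse ACR and NGAL on the log scale. This is a recommendation, not the correction of an error.

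The cost is a few sentences and little extra analysis. Blood is already drawn at 6 h and baseline values are already collected. Neither the number of visits nor the sample size changes.
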